##### Suicidal behaviour

In order to investigate the effects of MCT on suicidal behaviour, time to first suicidal event, including suicide attempts and suicide completions, over the 1-year follow-up study period will be investigated.

##### Functioning

Functioning will be recorded through the Global Assessment of Functioning (GAF) [42], the World Health Organization Disability Schedule (WHODAS) [43] and the Satisfaction Life Domains Scale (SLDS) [44]. In addition, as a relatively novel methodology in patients with psychotic disorders, ecological momentary assessment (EMA) [27] will be piloted in a subsample of those participants who agree to set up two web-based applications in their smartphones, namely Memind (www.memind.net) and eB2 [28]. Memind is an ‘active’ platform which has two different interfaces or views, namely staff and patient view. The ‘electronic health record’ allows staff to electronically record data on sociodemographic, diagnostic and pharmacological variables, while the patient view was designed in order for patient to self-rate some scales such as the BCIS [10], which will be one of the primary outcome measures in this RCT as detailed above. On the other hand, Evidence-Based Behavior (eB2) is a ‘passive’ platform designed for recording functioning-related data, such as mobility, i.e., location, distance, speed; physical activity i.e., number of steps, sleep data; social activity, i.e., phone use, active apps, social network data and emotions, i.e., prosodic analysis of speech signals and text message emotion analysis), without the subject’s collaboration (it is ‘passive’). Data are anonymised and sent to a secure server. Memind and eb2 will be combined to create a machine learning mental health system allowing a continuous feedback from digital phenotyping [45].

#### Additional variables

##### Demographic and clinical data

At baseline data on the following demographic and clinical variables will be collected: gender, age at the study inception, nationality, ethnicity, marital status, education level, living status, employment status, ICD-10 diagnosis, duration of untreated psychosis (which will be estimated with the Nottingham Onset Schedule, [46], number of previous admissions, number, date and method of previous suicidal acts, current medications, alcohol/illicit drugs dependence (present/absent, medical comorbidities (present/absent) family history of mental illness (present/absent).

Marital status, living status and employment status will be reassessed at 1-year follow-up as measures of functioning.

##### Premorbid adjustment

Premorbid adjustment, which can be defined as ‘the degree of achievement of developmental goals’ will be retrospectively rated with the Premorbid Adjustment Scale (PAS) [47]. Specifically, the PAS provides scores on the level of adjustment over i) childhood (to age 11), ii) early adolescence (age 11–15), iii) late adolescence (age 15–17) and iv) adulthood (age ≥ 18). With regard to childhood and adolescence, items inquiry about sociability and social withdrawal, peer relationships, scholastic performance, adaptation to school and ability to form socio-sexual relationships. The questions regarding adulthood focus on social relationships by asking about educational achievement, social relationships and level of interest in, and enjoyment of, major life activities, such as work or family.

##### Neurocognition

The neurocognitive assessment battery, which will be administered at the three assessments, will include the short version of the Wechsler Adult Intelligence Scale (WAIS) Revised [30], which estimates current intelligence quotient (IQ), and the Trail Making Test (TMT) [31], which assesses executive function. Subtracting time in seconds to complete TMT task B minus time in seconds to complete TMT task A gives a measure of executive function, whilst controlling for processing speed.

##### Metacognition

Three metacognitive tasks will be completed by participants at the three assessments (T0, T1, T2):
Jumping to Conclusions (JTC) will be determined with the beads task [48].During this task, the individual is asked to decide the jar to which the extracted bead belongs on the basis of probability (in task 1 the probability is 85:15, while in task 2 the probability is 60:40). ‘JTC’ is considered as making a decision after extracting one or two beads.The Hinting Task [49, 50] will be used to measure Theory of Mind (ToM) performance. Learning is avoided by using different stories at the three assessments. Cronbach’s α was good (0.64) for the Spanish version [37].In addition, the Emotional Recognition Test Faces [51], which is composed of 20 different pictures representing people’s emotions, will be used to evaluate ToM.

### Intervention

Participants will be randomised either to receive (in addition to their usual treatment, including antipsychotic medication) MCT or to attend a support group. Both ‘interventions’ are implemented for the same duration (one session per week lasting for about 45–60 min over 8 weeks). Unlike comparing MCT with ‘treatment as usual’ (TAU), controls will attend a weekly support group to avoid group attendance-related biases, consistent with some previous RCTs on MCT [37].

#### Metacognitive training (MCT)

Metacognitive Training (MCT) was first developed in Germany in 2007 by Steffen Moritz and Todd Woodward [13] targeting positive psychotic symptoms of patients with schizophrenia. In short, MCT seeks ‘to plant the seeds of doubt’ regarding cognitive biases leading to delusional thoughts rather than asking patients to talk about of their problems, which is likely to be distressful, particularly within the context of a group. MCT consists of ten group sessions focused on different topics (Modules) as follows: Attributional Style (Module 1), Jumping to Conclusions (Modules 2 and 7), Changing Beliefs (Module 3), Empathy (Modules 4 and 6), Memory (Modules 5), Depression and Self-Esteem (Module 8) and two additional modules, namely Self-Esteem (Module 9) and Stigma (Module 10). Modules 8 (Self-Esteem), 9 (Self-Esteem) and 10 (Stigma) can be delivered together as one session so the intervention totals eight weekly sessions, that is, 8 weeks. The therapists who will deliver MCT to participants of this RCT ([name] and [name]) undertook training from one of the co-authors of the Spanish version of the MCT manual ([name]), which is available at: http://www.uke.de/mkt and was directly supervised by Steffen Moritz.

#### Support group

Controls will attend eight weekly support groups. In line with the ‘treatment as usual’ delivered to most patients with psychosis in our clinic, seven sessions will focus on the following topics: 1) basic activities of daily living (BADL), 2) instrumental activities of daily living (IADL), 3) physical health, 4) press-based work, 5) psychoeducation on emotions, 6) psychoeducation on illness, 7) social and family relationships. One additional session will give participants some time to openly raise general issues and concerns which were not discussed during the above sessions. In order to minimise the effect of this ‘intervention-like’ on controls, the interaction/input from the therapists ([name] and [name]) will be minimal. Thus, controls will be encouraged to attend these group sessions, from which they can benefit. While not an intervention as such, this should turn into enough incentive to reach similar attendance rates in both arms of the RCT.

Treatment fidelity will be looked at by recording a random selection of MCT sessions (after obtaining consent from participants), which will be independently assessed against the manual criteria (http://www.uke.de/mkt) by two researchers from our group ([name] and [name]) with no involvement in the assessments or interventions. These two researchers will also determine whether controls may have been significantly exposed to elements of metacognition by accident during the group sessions.

In addition to the randomisation group intervention, all participants will have full access to their treatment so they are expected to continue taking medication and receiving non-metacognitive-based psychotherapies as recommended by the treating multidisciplinary team. This will also allow early identification of potential adverse events, unintended effects of the trial and trial misconduct.

### Statistical analysis

Participants’ data will be analysed at the end of the study on an intention-to-treat (ITT) basis, thus including all patients with baseline information available. Imputation methods will be used to estimate missing values. All the analyses will be performed with the Statistical Package for Social Science version 25.0 (SPSS Inc., Chicago, IL, USA).

First, demographic and clinical characteristics of groups (MCT and controls), including insight measures, will be compared at baseline so parametric and non-parametric tests will be used as appropriate. Also, for descriptive purposes, between-arm completion rates differences will be analysed at the end of the study.

Second, in order to investigate the primary outcome of the study, namely insight changes over the trial period, univariate analysis of covariance (ANCOVA) models will examine between-group differences (MCT and controls) in the SAI-E and BCIS total and subtotal scores changes from T0 to T1 and from T0 to T2 (as the dependent variable), whilst adjusting for baseline data. Hence, the effects of treatment (independent of time) and treatment group allocation*time interactions on insight changes will be investigated. We will also explore within-group scores changes between T0, T1 and T2. Specifically, we will estimate effect sizes (Cohen’s *d*) and the corresponding 95% confidence intervals (CI) from the imputed datasets for between- and within-group insight scores changes. In accordance with Cohen’s conventions [52], effect sizes will be classified as ‘small’ (*d < 0.2),* ‘medium’ *(d* = 0.2–0.5) or ‘large’ (*d* > 0.8). Due to multiple testing and the subsequent risk of type I error, results will be adjusted using Bonferroni correction.

Third, for the secondary outcomes evaluated with continuous variables, i.e., symptom severity (PANSS and CDSS) and functioning (GAF, SDLS and WHODAS), analogous ANCOVA models will be used. For those binary secondary outcomes, namely suicidal behaviour and readmissions, survival analyses, i.e., multivariable Cox regression models [53], will model time to the outcome event (i.e., first suicidal event or hospital admission, respectively) or the censoring date as appropriate, whilst adjusting for baseline variables.

Finally, variables inter-relationships over the trial period will be examined by means of path analysis through structural equation modeling, thus testing the effect of putative mediators/moderators/confounders/covariates, including neurocognition measures, on the above associations.

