### Randomisation and assessor-blindness

After the baseline (T0) assessment participants are randomised to either MCT or the support group, both of which are run by [name] and [name], through a computerized plan (no stratification factors) in blocks of 10 subjects (maximum number of each group) and assessor ([name])-patient blind. Only one co-principal investigator of the project ([name]) has access to the randomisation plan, but the assessor ([name]) is not informed of the patient’s allocation group, thus ensuring assessor-blindness since the patient may find out what intervention he/she is receiving, for which the study cannot be considered to be double-blind, although it is ‘single-blind’, that is, ‘assessor-blind’. Also, big efforts will be made on the ground to reduce the risk that the assessor ([name]) may become accidentally unblinded and patients are reminded that they should not disclose their group assignment at any time. At the end of the baseline assessment, participants receive an envelope with the intervention assignment from an independent administrator who is not involved in the research team. A reminder mobile text-message is also sent to participants within the next 24 h with the group details (date, time and venue), which is also re-sent again during the 24 h prior to the appointment, which is very similar to our routine clinical practice. Hence, assessor-blindness is guaranteed at all times throughout the study period since the assessor ([name]) is not involved in the randomization plan or the active interventions. See the CONSORT flowchart in Fig. 1, below, for details.

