#### Power calculations and estimation of sample size

Given that the mean SAI-E score for psychosis patients is 13/28 with a standard deviation of around 6 [32, 35], a difference of 2 points (e.g., 13 vs. 15) between groups (e.g., MCT vs. controls), which is considered to be clinically meaningful [26], is equivalent to an effect size of 0.33 with a two-tailed alpha significant level set at 5%. Under these assumptions, for reaching a sufficient statistical power of β = 80% at the end of the study, we will need *n* = 63 subjects in each arm, that is, a total sample size of *N* = 126 patients, who will be analysed at the end of the study on an intention-to-treat (ITT) basis. Attrition rates in previous RCTs investigating MCT effects on symptoms were low (approximately 10%) [18]. However, since we will follow-up patients over a more prolonged period (1 year) we have conservatively assumed a much higher drop-out rate of 50%. Under this assumption, the study will be carried out with an initial sample size of *N* = 252 patients, i.e., *n* = 126 participants in each group/arm at the study inception, which will also allow both ITT and ‘per protocol’ analyses with sufficient power. See the CONSORT flow chart in Fig. 1 for details.

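### Both arms are treated in therapy groups of at most 10, but the primary ANCOVA treats patients as independent; if outcomes correlate within groups, its standard errors are too small

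*Protocol article*

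**What the plan says.** All references are to the protocol article.

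- **Delivery, MCT arm.** Metacognitive training (MCT): "MCT consists of ten group sessions focused on different topics", condensed to eight weekly meetings.
- **Delivery, control arm.** Support group: "Controls will attend eight weekly support groups".
- **Group size.** Randomisation and assessor-blindness: patients are randomised "in blocks of 10 subjects (maximum number of each group"). Ten is therefore a ceiling.
- **Leaders.** The same section says patients go to "MCT or the support group, both of which are run by" the same two therapists.
- **Primary model.** Statistical analysis: "univariate analysis of covariance (ANCOVA) models will examine between-group differences (MCT and controls") in SAI-E and BCIS changes from T0 to T1 and from T0 to T2, adjusted for baseline. On multiplicity, "results will be adjusted using Bonferroni correction"; the number of tests is not given. Secondary continuous outcomes get analogous ANCOVAs, and admissions and suicidal events get Cox models.
- **Sample size.** Power calculations and estimation of sample size: "a difference of 2 points (e.g., 13 vs. 15) between groups", SD about 6, 80% power, "with a two-tailed alpha significant level set at 5" per cent. This leads to 63 per arm at the end of the study and 126 per arm at inception, allowing for 50% loss.

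No section has a random effect, a cluster-robust error or a covariate for therapy group, and the sample size has no ICC or design effect.

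**The concern.** Patients who spend eight weekly sessions in the same room influence each other and share whatever happened in that room. Their outcomes may then be more alike than those of patients from different groups in the same arm. Individual randomisation does not prevent this, because the clustering arises after allocation.

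A support group for controls balances the average effect of attending a group. It does not remove correlation among members of one group.

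An ordinary ANCOVA assumes independent residuals. With positive within-group correlation it understates the standard error of the treatment effect, so confidence intervals are too narrow and p-values too small. The Cox models for the secondary outcomes share the assumption. This is not detail left for an analysis plan, because the protocol names a specific primary model that rests on independence.

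**Working it through.** **1. The plan's own sample size.** For two means, n per arm = 2(1.96 + 0.84)² × SD² / difference². With SD 6 and difference 2 this gives 142, not 63; 63 corresponds to a standardised difference of 0.5. That is a separate matter. The dropout step does reproduce: 63 / (1 − 0.5) = 126 per arm. What matters here is that neither step contains a design effect.

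**2. Inputs.**
- Group size at most 10, 126 enrolled per arm, 50% loss, two-sided 5%: from the protocol.
- Analysed per group, m: about 10 × 0.5 = 5 when 63 per arm remain; up to 10 only if nearly all 126 per arm are analysed. Either way there are about 13 groups per arm (63/5 or 126/10).
- ICC of the baseline-adjusted outcome: not in the documents. Assumed range 0.02 to 0.10.

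**3. Formulas.** Design effect DE = 1 + (m − 1) × ICC. The ANCOVA standard error is 1/√DE of the true one. Actual two-sided error = 2 × [1 − Φ(1.96/√DE)]. Effective sample = n/DE. A correct interval is wider by √DE − 1.

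**4. Same ICC in both arms.**

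| m | ICC | DE | Actual error of a 5% test | Interval wider by | Effective n per arm |
|---|---|---|---|---|---|
| 5 | 0.02 | 1.08 | 5.9% | 4% | 63/1.08 = 58 |
| 5 | 0.05 | 1.20 | 7.4% | 10% | 63/1.20 = 52.5 |
| 5 | 0.10 | 1.40 | 9.8% | 18% | 63/1.40 = 45 |
| 10 | 0.02 | 1.18 | 7.1% | 9% | 126/1.18 = 107 |
| 10 | 0.05 | 1.45 | 10.4% | 20% | 126/1.45 = 87 |
| 10 | 0.10 | 1.90 | 15.5% | 38% | 126/1.90 = 66 |

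At ICC 0 every row returns 5%. At ICC 0.01 the error is 5.5% (m = 5) or 6.1% (m = 10).

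**5. Clustering in the MCT arm only.** The relevant DE is the average of the two arms, (1 + DE)/2. For m = 5 it is 1.04 to 1.20, giving an error of 5.5% to 7.4%. For m = 10 it is 1.09 to 1.45, giving 6.1% to 10.4%.

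**6. Simulation.** The planned ANCOVA was simulated under no treatment effect, with 8,000 runs per setting and an assumed baseline–outcome correlation of 0.6.
- Groups of 5, ICC 0, 0.02, 0.05 and 0.10: error 4.7%, 5.7%, 7.9% and 9.7%.
- Groups of 10, same ICCs: 4.6–5.1%, 7.0–7.2%, 9.8–9.9% and 15.3–15.9%.
- An analysis of therapy-group means held 4.8% to 5.4% throughout.

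**7. Bonferroni.** It presumes that each p-value is valid. With two tests at 2.5% (critical value 2.24), each actually runs at 3.1%, 4.1% and 5.8% for m = 5, and at 3.9%, 6.3% and 10.4% for m = 10, at ICC 0.02, 0.05 and 0.10.

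**The case against.** The strongest reply is that the harm rests on an ICC that nobody has stated. That stands: at ICC 0 the ANCOVA is valid, and a reader who infers that the type I error is certain to exceed 5% goes further than the documents allow.

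There are also reasons to expect modest clustering. MCT follows a manual with fidelity checks and avoids asking patients to discuss their own problems, and therapist input to the control groups is meant to be minimal. This supports the lower part of the range and the MCT-only case in step 5. It does not support assuming zero, and one control session is an open discussion whose content will differ by group.

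A reader might blame shared leaders. The documents do not support that: the same therapists run both arms, so a leader effect largely cancels. What remains is shared membership and sessions. The protocol does not say that groups are closed cohorts, so stable membership is itself an inference.

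A reader might also pair full groups of 10 with 63 per arm and conclude that, at ICC 0.05, 63 patients are worth 63/1.45 = 43. That does not fit the plan. If 126 per arm are enrolled and half are lost, 63 per arm means about 5 per group. Ten per group goes with about 126 per arm. If each block of ten were split five and five, groups would start at five and be smaller still after loss.

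Bonferroni is conservative for correlated outcomes, so at a very small ICC the family-wise error could stay near 5%. It does not correct the standard errors. The path analysis concerns mediators, moderators and confounders, and does not address clustering either.

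**Conclusion.** The point holds in conditional form. The protocol fixes a primary model that assumes independence for patients treated in groups in both arms. Given any positive within-group correlation, the error is in the anti-conservative direction.

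On an assumed ICC of 0.02 to 0.10 in both arms, the case that fits 63 analysed per arm is an actual error of about 6% to 10%; at ICC 0.05, 63 patients are worth about 52 to 53. The range of about 7% to 16% applies only when nearly all 126 per arm are analysed in full groups of 10, as the imputed intention-to-treat analysis would have it; at ICC 0.05, 126 are then worth about 87. The upper figure should not be read as the expected one.

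This is a cheap improvement, not a reason to discount the trial.

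**What to change.** - Record the allocated therapy-group identifier for every patient in both arms while the trial runs, since it may be hard to recover later.
- Replace the ANCOVA with a baseline-adjusted linear mixed model that has a random intercept for allocated therapy group in both arms and Satterthwaite or Kenward-Roger degrees of freedom, because there are only about 13 groups per arm. Keep patients who do not attend in their assigned group.
- Use standard errors clustered on therapy group for the secondary Cox models.
- Restate the power with a design effect over a stated ICC range.

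The cost is one more database variable and some analysis wording. Intervals become wider by about 4% to 18% at 5 analysed per group, and by up to 38% at 10 per group with ICC 0.10. The stated power will be lower.

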### Outcome measures

#### Co-primary outcomes

Insight is the primary outcome of this RCT and both clinical and cognitive insight will be considered.
*Clinical insight* will be measured with the Spanish version [33] of the Schedule for Assessment of Insight, expanded version (SAI-E) [26]. The SAI-E takes the form of a semi-structured interview which enquires about different aspects of insight and provides scores on three insight dimensions in line with David’s model [23] - illness recognition, symptom relabeling, treatment compliance - and a total insight score. The scale was found to be easily applicable in routine clinical practice [34] and good to excellent inter-rater reliability was reached, with total insight scores intra-class correlations coefficients ranging from 0.92 to 0.98 (*p* < 0.001) [35]. [name] received training from the scale author ([name]) and they both co-led the validation study of the SAI-E Spanish version [33], which will be used in this RCT.*Cognitive insight* will be assessed by the Spanish version [36] of the Beck Cognitive Insight Scale (BCIS) [10], which is a 15-item self-administered scale which evaluates self-reflectiveness (9 items) and self-certainty (6 items). A composite index can thus be calculated by subtracting self-certainty from self-reflectiveness. Internal consistency was found to be acceptable (Cronbach’s α = 0.60–0.68) [37].

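### The stated 80% power is for one SAI-E comparison at an unadjusted 5%, but the primary analysis is a Bonferroni-corrected set of SAI-E and BCIS comparisons at two time points

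*Protocol article*

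**What the plan says.** All references are to the protocol article.

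- **Co-primary outcomes.** The section states that "Insight is the primary outcome of this RCT and both clinical and cognitive insight will be considered". The SAI-E yields "illness recognition, symptom relabeling, treatment compliance - and a total insight score", so four scores. The BCIS has two subscales, self-reflectiveness and self-certainty, and "A composite index can thus be calculated by subtracting self-certainty from self-reflectiveness", so three scores.
- **Statistical analysis.** The primary outcome is examined with ANCOVA models of "SAI-E and BCIS total and subtotal scores changes from T0 to T1 and from T0 to T2", adjusted for baseline. Group-by-time interactions and within-group changes are also to be examined. Because of multiple testing, "results will be adjusted using Bonferroni correction". The number of tests to divide by is not given.
- **Power calculations and estimation of sample size.** The calculation takes one SAI-E difference of 2 points with an SD of about 6, "with a two-tailed alpha significant level set at 5" per cent, and 80% power. It arrives at 63 analysed per arm, and 126 per arm randomised after allowing for 50% dropout. The BCIS, the second time point and the Bonferroni correction do not enter it.
- **Background.** The main aim concerns clinical and cognitive insight over a one-year follow-up. No section names one score or one time point as decisive.

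**The concern.** A power statement is useful only if it describes the test that will decide the trial. Here the analysis section commits to several primary comparisons at a reduced alpha, while the sample size section assumes one comparison at the full 5%. Both statements are in the article, so this is a conflict between two things the plan fixes and not a detail left for later.

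Two things are at stake. First, the chance of confirming the SAI-E effect on which the trial was sized is lower than claimed, by an amount that depends on an unstated divisor. Second, with neither the family nor the decisive time point fixed, the correction could be sized after the results are known, and a reader could not tell which result counts as success.

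**Working it through.** **Inputs.** Difference 2 points, SD 6, two-sided 5%, 80% power, 63 per arm analysed, 126 per arm randomised (sample size section). Scores: 3 + 1 for the SAI-E and 2 + 1 for the BCIS (Co-primary outcomes). Intervals: T0–T1 and T0–T2 (Statistical analysis).

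**Number of primary comparisons.** (4 + 3) scores × 2 intervals = 14, before any interaction or within-group test. Bonferroni over 14 gives 0.05/14 = 0.00357. The smallest possible family, two tests, gives 0.05/2 = 0.025.

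**The plan's own figure.** d = 2/6 = 0.333. The normal approximation is n per arm = 2 × 6² × (1.960 + 0.842)² / 2² ≈ 141.3, so 142; the t-test gives 143. The stated 63 is not reproduced. It corresponds to d = 0.5, because 2 × 6² × (1.960 + 0.842)² / 3² ≈ 62.8. The dropout step does reproduce: 126/(1 − 0.5) = 252.

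**Power for the SAI-E comparison.** Two-sample noncentral t with 2n − 2 degrees of freedom and noncentrality d × √(n/2). This is 0.333 × √31.5 = 1.87 at 63 per arm, 0.333 × √63 = 2.65 at 126 per arm, and 0.5 × √31.5 = 2.81 for d = 0.5 at 63 per arm.

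| Setting | alpha 0.05 | alpha 0.05/2 | alpha 0.05/14 |
|---|---|---|---|
| 63 per arm, d = 0.5 (multiplicity alone) | about 80% | about 70% | 44% |
| 63 per arm, d = 0.333 | 46% | 35% | 14% |
| 126 per arm, d = 0.333, no dropout | 75% | 65% | 39% |

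The first row isolates multiplicity by granting the plan its claimed 80%. The other two rows use the plan's own effect size.

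**Allowing for ANCOVA.** Baseline adjustment reduces the residual SD to 6 × √(1 − ρ²), where ρ is the baseline-to-outcome correlation. The article gives no value, so the following is an assumed range.

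| ρ (assumed) | 63 per arm, 0.05/2 | 63 per arm, 0.05/14 | 126 per arm, 0.05/2 | 126 per arm, 0.05/14 |
|---|---|---|---|---|
| 0.3 | 38% | 16% | 70% | 44% |
| 0.5 | 46% | 22% | 79% | 55% |
| 0.7 | 64% | 37% | 93% | 78% |

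At the planned analysed size of 63 per arm, every entry is below 80%.

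**The case against.** Several points limit how far this can be taken.

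- **The 14% is not the price of multiplicity.** A reader might set 14% against the claimed 80% and blame the correction. Of that 66-point gap, 34 points (80% to 46%) exist before any correction, because 63 per arm does not follow from the stated inputs. That is a separate error.
- **The divisor of 14 is a count and not a stated rule.** The text says only that results will be Bonferroni-adjusted, and a fuller plan may define the family. That is fair. The conflict with the sample size section does not depend on 14, though; it begins at a divisor of 2.
- **ANCOVA recovers power.** It does, and unadjusted figures alone would overstate the loss. With 126 per arm and no dropout, ρ of 0.7 gives 93% at 0.05/2. But the sample size section claims no such gain, and 126 per arm requires every randomised patient to be observed.
- **Both scales must succeed.** The term co-primary might suggest this. The text says only that "both clinical and cognitive insight will be considered" and states no joint rule; the Bonferroni correction points instead to success on either scale.
- **Inflated type I error.** A reader might infer a familywise error of 1 − 0.95^14 = 51%. That needs 14 independent, uncorrected tests. The plan corrects, and the scores overlap by construction. A full Bonferroni correction would be conservative.
- **The figures are for one comparison.** The chance that at least one of 14 tests is significant is higher than the per-test power if several effects are real. It cannot be computed from the article, and it is not the quantity that the sample size section claims to provide.

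**Conclusion.** The point holds in this form: the stated 80% power does not apply to the stated primary analysis under any Bonferroni family of two or more tests, and no planning figure is given for the BCIS. The loss from multiplicity alone is about 10 percentage points for two tests (80% to 70%) and about 36 for 14 tests (80% to 44%), granting the plan its 80% at 63 per arm. With the plan's own d = 0.333, power for the SAI-E comparison at 63 per arm is 35% or 14% without baseline adjustment. It is 38–64% or 16–37% for assumed baseline correlations of 0.3 to 0.7. These figures rest on an SD of 6, equal arms and, for the last column of each table, a family of 14 inferred from the text. The documents do not support a claim that the plan leaves type I error uncontrolled, or that it requires both scales to succeed.

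**What to change.** 1. Fix the primary family in advance as two tests: SAI-E total and BCIS composite at one named time point. T2 fits the one-year aim in the Background, although the analysis section treats both intervals alike, so the sponsor should confirm the choice.
2. State the success rule: success on either scale, with Holm or Hochberg at an overall two-sided 0.05. The smaller p-value is tested at 0.025 under Holm, so the 0.05/2 figures are a floor for each scale's power.
3. Make the other time point, the subscales and the within-group changes secondary, outside the primary family.
4. Restate power at the alpha actually used, giving the assumed baseline correlation and a planning assumption for the BCIS. Correct the 63-per-arm figure in the same step: adjusting alpha from that base alone would still leave the trial too small. Without baseline adjustment, d = 0.333 needs about 143 per arm at 5%, and more at 0.025.

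Cost: items 1 to 3 are wording, and the T1 and subscale results become secondary. Item 4 is one recalculation, but it will show power below 80% at the planned size unless a high baseline correlation holds. The sponsor must then either enlarge the target or report the lower power openly.
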